#### Canadian occupational performance measure performance score

The best possible score for COPM-P is 10 points. Any participant with a score of 10 at baseline will be excluded from the modified intent-to-treat (mITT) population, since the condition of interest is absent in these participants. Gains of at least 2 points in COPM are considered clinically important (MCID; 27–30). Using this threshold, participants will be classified as either a responder (change in COPM-P of ≥ 2) or non-responder (change in COPM-P of < 2) at weeks 8 and 12. The proportion of responders at each time point will be summarized by treatment group. Responder analysis will be performed for the intent-to-treat (ITT), mITT, per protocol (PP) populations, and also the subset of participants with a baseline score of ≤ 8 (since participants with a baseline score of > 8 cannot meet the MCID).

For ANCOVA and logistic regression, a hierarchical testing procedure will be used to maintain the Type I error rate at 5%. Firstly, the statistical significance of Revitive Medic^©^ Program 1 versus Revitive sham will be calculated, and if the *p*-value is ≤ 0.05 testing will proceed to Revitive^®^ Program 2 versus Revitive sham (also at the 5% significance level). If Revitive Medic^©^ Program 1 versus Revitive sham has a *p*-value of > 0.05, then the difference between Revitive^®^ Program 2 and Revitive sham will be considered non-significant but a *p*-value will be presented for descriptive purposes.

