### Outcomes {12}

The primary endpoint for the study comprises a comparison of change in Canadian Occupational Performance Measure Performance (COPM-P) score from baseline to Week 8 for Revitive Medic^©^ Program 1 versus Revitive sham. COPM-P score is a self-evaluation measure of each participant’s current physical/ occupational performance status.

Secondary endpoints comprise:Change in COPM-P from baseline to week 12, comparing Revitive Medic^©^ Program 1 versus Revitive sham.Change in COPM-P from baseline to weeks 8 and 12 comparing Revitive^®^ Program 2 and Revitive sham.Change in Canadian Occupational Performance Measure Satisfaction (COPM-S) score from baseline to week 8, comparing Revitive Medic^©^ Program 1 versus Revitive sham and Revitive^®^ Program 2 versus Revitive sham. COPM-S score is a self-evaluation measure of each participant’s current satisfaction with their relevant physical/occupational performance.Change in leg pain from baseline to weeks 8 and 12, comparing Revitive Medic^©^ Program 1 versus Revitive sham and Revitive^®^ Program 2 versus Revitive sham; participants will rate leg pain using an 11-point numerical rating scale.Change in blood flow volume and intensity from baseline during device use, comparing Revitive versus Revitive sham.Change in symptom score from baseline to weeks 8 and 12 in terms of overall symptom score and each item (heaviness, tiredness, aching, and cramps), comparing Revitive Medic^©^ Program 1 versus Revitive sham and Revitive^®^ Program 2 versus Revitive sham.

Assessments conducted at the different study visits are presented in Table 1.

**Table 1 Tab1:** Study assessments in the NMES stimulation trial

	**Telephone assessment (≥ week − 1)**	**Baseline assessment** **(week 0)**	**Treatment period**	**Week 8**	**Week 12**
Eligibility	x	x			
Randomization	x				
Informed consent		x			
Demographics		x			
Medical history	x	x	x	x	x
Medications	x	x	x	x	x
Device issue and familiarization		x			
Device usage		x	x	x	
COPM		x		x	x
Symptom (heaviness, aching, tiredness, and cramps) scores		x		x	x
Leg pain		x		x	x
Doppler ultrasound		x		x^a^	
Adverse events		x	x	x	x

^a^For participants with poor quality Doppler data at week 0

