### Sample size {14}

The sample size for the study is 117 participants, with 39 participants in each treatment group.

At the time of protocol development, the anticipated effect of Revitive Medic^©^ Program 1, Revitive^®^ Program 2, and Revitive sham on the primary outcome (COPM-P) was not understood. Multiple publications [27–29] have cited an improvement of 2 points in COPM-P score for an individual participant as a minimally clinically important difference (MCID); a 2-point change in COPM was therefore set as the threshold required for a participant to be considered a responder to the study intervention.

An absolute difference of 30% in the proportion of participants that meet the COPM-P responder definition (improvement of 2 points) between Revitive sham and Revitive Medic^©^ Program 1 or Revitive^®^ Program 2 was considered necessary to demonstrate a clinically meaningful difference for either test device. To control Type I error, a single primary endpoint was chosen namely the difference between Revitive sham and Revitive Medic^©^ Program 1; a comparison of Revitive sham and Revitive^®^ Program 2 is a secondary endpoint. A sequential testing procedure will be employed such that the secondary endpoint can only be formally assessed if the primary endpoint achieves statistical significance (*p* < 0.05).

Basing the sample size calculation on this design, it was determined that 39 participants would be needed in each of the three intervention groups to show an absolute difference of 30% in the proportion of responders between Revitive sham and Revitive Medic^©^ Program 1 or Revitive^®^ Program 2 at 80% power and two-sided 5% significance. For the purposes of the power calculation, the comparison used a Pearson chi-square test at the two-sided significance level (*p* < 0.05).

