## Statistical methods

### Statistical methods for primary and secondary outcomes {20a}

Analysis of covariance (ANCOVA) will be used to compare Revitive Medic^©^ Program 1 versus Revitive sham and Revitive^®^ Program 2 versus Revitive sham at weeks 8 and 12, with change from baseline as the dependent variable, and treatment group and baseline value as independent variables. Least square means for each group, treatment differences, 95% confidence intervals (CIs) and *p*-values will be calculated. Model assumptions will be checked and, if departures from normality are evident, a Wilcoxon rank sum test and associated 95% CI using the Hodges Lehmann estimator will be used to compare groups.

Logistic regression with baseline value as a covariate and treatment group as a classification variable will be used to compare the proportion of responders in each test group versus the sham group. Treatment effect will be estimated as an odds ratio (test/sham), with 95% CIs and associated *p*-value. An odds ratio of > 1 indicates a better outcome in the test group.

For all parameters at each time-point, only participants with both a baseline and the corresponding post-treatment assessment will be included in the calculation of change from baseline.

Any subgroup analysis based on factors such as, for example, age or co-morbidities in a study of this size (< 40 per group) is going to have limited power to show differences within these subgroups. Therefore, any such analysis will be of limited value. However, further exploratory analyses, investigating the effects of other covariates (such as age and BMI), may be undertaken for the study outcomes and provided as supportive information.

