#### Leg pain

Any participant who has no pain (pain score of 0) at baseline will be excluded from the mITT analysis since the condition of interest is absent. A change in pain score of 2 (measured on an 11-point numerical rating scale) is recognized as meaningful [37–39]; participants will, therefore, be classified as responders if their pain score improves by at least 2 points from baseline. The proportion of responders at Weeks 8 and 12 will be summarized by treatment group. The hierarchical test procedure will be used to evaluate the effectiveness of Revitive Medic^©^ Program 1 and Revitive^®^ Program 2. Responder analysis will be performed for the ITT, mITT, PP, and also the subset of participants with a baseline pain score of ≥ 2 (since participants with a baseline score of < 2 cannot meet the criteria for a clinically meaningful change).

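### The 5% Type I error claim covers both ANCOVA and logistic regression of COPM-P, but the hierarchy orders only the two devices, and the sections conflict on which analysis decides success

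*Protocol article*

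**What the plan says.** All references are to the protocol article.

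- **Outcomes {12}** defines the deciding outcome in these words: "The primary endpoint for the study comprises a comparison of change in Canadian Occupational Performance Measure Performance (COPM-P) score from baseline to Week 8". The comparison is Program 1 against sham. Responder status is not in the list of primary or secondary endpoints.
- **Statistical methods for primary and secondary outcomes {20a}**: two analyses are planned. One is ANCOVA, "with change from baseline as the dependent variable, and treatment group and baseline value as independent variables". The other is logistic regression with baseline as covariate, which "will be used to compare the proportion of responders in each test group versus the sham group"; here "Treatment effect will be estimated as an odds ratio (test/sham), with 95% CIs".
- **Canadian occupational performance measure performance score**: "For ANCOVA and logistic regression, a hierarchical testing procedure will be used to maintain the Type I error rate at 5"%. Program 1 versus sham comes first; if p is at most 0.05, Program 2 versus sham follows, "also at the 5% significance level".
- **Sample size {14}**: 39 per group gives 80% power at two-sided 5% for a 30-point difference in the proportion gaining 2 points, a difference described as necessary for clinical meaning. "For the purposes of the power calculation, the comparison used a Pearson chi-square test at the two-sided significance level". The section says one primary endpoint was chosen to control Type I error, but identifies it only by the device comparison, not by scale or test.
- **Trial design {8}** and **Sample size {14}**: Program 2 is formally tested only if the primary endpoint is significant.
- **Section {20c}** on non-adherence and missing data: mITT and PP analyses are secondary, which leaves ITT as primary.
- **Leg pain**: "The hierarchical test procedure will be used to evaluate the effectiveness of" the two programs there as well.

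**The concern.** A fixed sequence protects the 5% level only along the chain of hypotheses it orders. Here the chain runs over devices. ANCOVA and logistic regression each have their own chain, each starting at the full 5%, and nothing orders them or shares alpha between them. The sentence claiming 5% nevertheless names both analyses.

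The sample size section adds to the doubt. A reader of the endpoint list would take the change score as decisive; a reader of the sample size section would take the responder proportion. If the two disagree at week 8, the sections give different answers on whether the trial has succeeded and whether Program 2 may be tested. What is at stake is a confirmatory claim resting on whichever analysis happens to be significant, reported as controlled at 5%.

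**Working it through.** **1. The plan's own figure.** Inputs from Sample size {14}: 30-point difference, 80% power, two-sided 5%, Pearson chi-square. The sham responder rate is not stated (Interim analyses {21b} says only that it came from the pilot), so it is an assumption here.

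n per group = [1.960·√(2·p̄·(1−p̄)) + 0.842·√(p₁(1−p₁) + p₂(1−p₂))]² / (p₂−p₁)²

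At an assumed 20% vs 50%: [1.960·√0.455 + 0.842·√0.41]² / 0.09 = (1.322 + 0.539)² / 0.09 = 38.5, so 39 (power 80.5%).

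| Assumed sham rate | n per group needed | Power at 39 |
|---|---|---|
| 10% | 32 | 87.9% |
| 15% | 36 | 83.8% |
| 20% | 39 | 80.5% |
| 25% | 41 | 78.3% |
| 35% (worst case) | 43 | 76.5% |
| 50% | 39 | 80.5% |

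The 39 is attainable, but it is a figure for the responder comparison, not for the change score.

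**2. Error within one analysis.** Program 2 is tested only after Program 1 succeeds, both at 5%, so each chain taken alone holds 5%. The device hierarchy itself is sound.

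**3. Error if either week 8 analysis may count (Program 1 versus sham).**
- Upper bound: 0.05 + 0.05 = 10%.
- If the tests were independent: 1 − 0.95² = 9.75%.
- The tests share the same data and are positively correlated, so the true figure is lower.

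It was simulated under no effect with 39 per arm and 20,000 runs per row. Both models were adjusted for baseline, and scores were bounded at 1 to 10. Baseline mean was 5 with SD 1.5, and change had slope −0.3 on baseline. These distributions are assumptions; the article gives none. Data were complete and the planned Wilcoxon fallback was not modelled.

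| Mean change | Residual SD | ANCOVA | Logistic | Either |
|---|---|---|---|---|
| 0 | 1.8 | 4.9% | 3.1% | 7.0% |
| 0.5 | 1.8 | 5.1% | 4.5% | 8.0% |
| 1 | 1.8 | 5.1% | 4.8% | 8.1% |
| 1.5 | 1.8 | 4.7% | 4.8% | 7.5% |
| 2 | 1.8 | 5.2% | 5.2% | 8.1% |
| 0.5 | 2.5 | 4.8% | 4.8% | 7.7% |

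Neither test alone exceeds about 5%; together they give 7 to 8%.

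**4. Power if ANCOVA alone is primary.** By the normal approximation, without baseline adjustment, 39 per arm gives 80% power for (1.960 + 0.842)·√(2/39) = 0.63 SD. The article states no SD or mean difference for COPM-P change and says the anticipated effect was unknown, so this cannot be turned into points. If change were normal with equal SDs, 20% vs 50% responders would mean a shift of 0.842 SD and about 96% power; sham rates of 10% and 25% would give 99.5% and 94.2%.

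**5. Cost of keeping both routes.** At 2.5% each (Bonferroni), the responder test at 20% vs 50% needs (2.241·√0.455 + 0.842·√0.41)² / 0.09 = 46.7, so 47 per group (44 to 52 for sham rates of 15% to 35%).

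**The case against.** The strongest reply is that the primary test can be read from the text. Outcomes {12} names change in COPM-P at week 8, section {20a} analyses change by ANCOVA, and section {20c} leaves ITT as the main population. Trial design {8} and Sample size {14} open Program 2 only on the primary endpoint. On that reading Type I error is 5%. This stands: the inflation is conditional, and the rule for Program 2 exists but is contradicted. It does not rescue the COPM-P sentence, which extends the claim to logistic regression, or the sample size section, which rests on the responder comparison. A separate analysis plan might settle the choice, but it would have to overrule what is stated here.

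Three stronger readings are tempting, and the documents do not support them.

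- A reader might infer much larger inflation by also counting week 12, COPM-S and leg pain. Those endpoints are labelled secondary, and the 5% statement sits under the COPM-P heading. The article claims no familywise control across secondary outcomes, and any combined rate would rest on correlations it does not give.
- A reader might object that ANCOVA can be significant well short of the 30-point difference. That is true of any test with 80% power. The planned chi-square does the same: 8/39 vs 16/39 is a 20.5-point difference with z = 1.96 and p = 0.0497.
- A reader might infer that the trial is underpowered for ANCOVA. Under the normal model above, power would exceed 80%. The mismatch is one of documentation, not a demonstrated shortfall.

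**Conclusion.** The concern holds in a limited form. The statement that the procedure keeps Type I error at 5% for ANCOVA and logistic regression is wrong as written, because the procedure orders devices and not analyses. The sections also conflict on which analysis decides success and opens Program 2.

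The size depends on the reading. If either week 8 analysis may count, the error for Program 1 versus sham is about 7 to 8%; that range depends on the assumed score distributions, but the 10% ceiling does not. If the ITT ANCOVA is the sole primary analysis, the error is 5%, and what remains is that the stated 80% power describes a different test. A flat statement that the trial fails to hold 5% would go further than the documents allow.

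**What to change.** 1. In Outcomes {12} and section {20a}, name the ITT ANCOVA of COPM-P change at week 8, Program 1 versus sham, as the sole primary analysis. This follows the endpoint already defined.
2. Use one fixed sequence: that test, then the same ANCOVA for Program 2 versus sham, each at two-sided 5%.
3. In the COPM-P subsection, limit the 5% claim to this sequence and remove logistic regression from it.
4. Label logistic regression, week 12, COPM-S and leg pain as supportive with nominal p-values, or append them to the sequence in a stated order. Make the wording under Leg pain agree.
5. In Sample size {14}, state that the 80% power applies to the supportive responder comparison.

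Optionally, report the responder risk difference with a 95% CI beside the odds ratio, so that it can be read against the 30-point difference.

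The cost is wording. No participants are added, which matters because Trial status reports recruitment complete; keeping both routes at 2.5% each would need about 47 per group at an assumed 20% vs 50%. The price is that the responder result no longer offers a second route to a confirmatory claim.

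### The COPM-P testing hierarchy orders the two devices but not the two analyses, so the stated 5% error rate does not extend across the ANCOVA and the responder regression together

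*Protocol article*

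**What the plan says.** Outcomes {12} names one primary endpoint: "The primary endpoint for the study comprises a comparison of change in Canadian Occupational Performance Measure Performance (COPM-P) score from baseline to Week 8", Program 1 against sham. Its list of secondary endpoints contains no responder endpoint.

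Sample size {14} states: "To control Type I error, a single primary endpoint was chosen namely the difference between Revitive sham and Revitive Medic^©^ Program 1". It does not name the measure there. The 39 per group comes from a 30-point difference in the proportion of responders, tested by Pearson chi-square. The same section lets Program 2 be formally assessed only once the primary endpoint is significant.

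Statistical methods {20a} gives two analyses. The ANCOVA is specified "with change from baseline as the dependent variable, and treatment group and baseline value as independent variables". The logistic regression "will be used to compare the proportion of responders in each test group versus the sham group". Both use the same score, since "participants will be classified as either a responder (change in COPM-P of ≥ 2) or non-responder (change in COPM-P of < 2) at weeks 8". The same cut-off applies again at the later visit.

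The subsection on the COPM performance score then sets the error control: "For ANCOVA and logistic regression, a hierarchical testing procedure will be used to maintain the Type I error rate at 5" per cent. Program 1 versus sham is tested first; if p is at most 0.05, "testing will proceed to Revitive^®^ Program 2 versus Revitive sham (also at the 5% significance level").

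**The concern.** A fixed sequence controls error over the hypotheses that stand in the sequence. Here the sequence contains devices only. The two analyses of one score run side by side, each at 5%, yet the 5% is stated for both. The rule refers to a single Program 1 p-value although there will be two, and does not say which of them opens the gate.

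Two things are at stake. First, if the two tests disagree, the article gives a reader grounds to treat either as decisive: the endpoint definition favours the ANCOVA, while the sample size favours the responder comparison. Secondly, Program 2 could be reached through the responder gate alone.

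**Working it through.** **1. The plan's own figure.** With pooled variance, two-sided 5%, 80% power and no continuity correction,

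n = [1.96·√(2·p̄(1−p̄)) + 0.8416·√(p₀(1−p₀) + p₁(1−p₁))]² / (p₁−p₀)².

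The sham rate is not given, so it is an assumption. At 20% v 50%, p̄ = 0.35 and n = (1.322 + 0.539)² / 0.09 = 38.5, hence 39 per group (power 80.5%). The mirror image, 50% v 80%, also gives 39; 25% v 55% gives 41. The stated 39 is reproduced, and it belongs to the responder comparison. The article gives no power for the ANCOVA.

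**2. What the rule orders.**

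| Section | What it fixes | What it leaves open |
|---|---|---|
| Outcomes {12} | Change in COPM-P at week 8 is primary | Which model carries the test |
| Sample size {14} | Program 1 v sham is the single primary; sizing on responders | The measure behind that single primary |
| Statistical methods {20a} | ANCOVA for change, logistic regression for responders | Rank of the two |
| COPM performance score | Program 1, then Program 2, for both models at 5% | Order of, or alpha split between, the models |

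**3. Program 1, no true effect, either test allowed to count.** Treating the two test statistics as bivariate normal with correlation ρ, the error is 1 − P(|Z₁| < 1.96 and |Z₂| < 1.96):

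| ρ | 0.50 | 0.70 | 0.75 | 0.80 | 0.90 |
|---|---|---|---|---|---|
| Error | 9.1% | 8.35% | 8.1% | 7.8% | 7.0% |

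Independent tests would give 1 − 0.95² = 9.75%. The documents do not give ρ, so I simulated it. Assumptions: 39 per arm, complete data, baseline mean 4.5 and SD 1.6, correlation of baseline with change −0.3, mean change 0.5 to 2.0 with SD 1.8 or 2.0, scores held to 1–10, and 6,000 trials per setting.

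| Responder rate (about) | ANCOVA alone | Logistic alone | Either | ρ |
|---|---|---|---|---|
| 20% | 4.2% | 4.3% | 7.3% | 0.69 |
| 31% | 5.2% | 5.2% | 8.4% | 0.76 |
| 40% | 4.8% | 4.7% | 7.3% | 0.78 |
| 50% | 5.3% | 5.0% | 8.0% | 0.79 |

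Under the global null this is also the error over both devices, because a Program 2 claim needs its Program 1 gate to open first.

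**4. Program 2 null, Program 1 effective.** Here a false claim means that Program 2 is significant in at least one model whose Program 1 gate has opened. With 8,000 trials per setting:

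| Mean change, SD | Program 1 effect | Either model | ANCOVA sequence only |
|---|---|---|---|
| 0.5, 1.8 | 1.5 points | 7.3% | 4.9% |
| 0.5, 1.8 | 4 points | 7.7% | 4.7% |
| 1.0, 2.0 | 1.5 points | 5.8% | 3.9% |
| 1.0, 2.0 | 4 points | 7.7% | 4.9% |

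**5. The Program 2 route.** Suppose the Program 1 ANCOVA gives p > 0.05 and the Program 1 logistic regression gives p ≤ 0.05. Applied to each model separately, the rule allows a formal Program 2 responder test. Under Sample size {14}, with the primary as defined in Outcomes {12}, Program 2 may not be formally tested. The two sections give opposite answers.

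**The case against.** The strongest reply is that the deciding test can already be worked out. Outcomes {12} makes change at week 8 the only primary endpoint, Statistical methods {20a} assigns change to the ANCOVA, and section {20c} makes the mITT and per-protocol analyses secondary. Together these point to the week-8 ITT ANCOVA, whose error is 5%. On this reading the hierarchy means only that within each model Program 1 precedes Program 2, and for that pair of devices 5% is correct. The Leg pain subsection applies the same device order, which fits this reading. The chi-square test in Sample size {14} is there for the power calculation only.

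Much of this stands. A reader might infer that the plan as written carries an 8% error. The documents do not support that: no section says that success on either test is enough, and the figure needs such a rule. Nor does a flat 8% hold for Program 2, whose error depends on which gates open.

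The reply does not rescue the sentence itself. It states one error rate for two analyses that the procedure does not order. The article expressly demotes other analyses (mITT and per-protocol as secondary, extra covariates as supportive, baseline carried forward as sensitivity) but not the logistic regression, to which it gives formal 5% testing. An SAP, not shown here, might rank the two. The point does not rest on missing detail, however: the article states the rule together with a property that the rule lacks.

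**Conclusion.** The concern holds in a conditional form. The stated 5% is true of the ANCOVA sequence alone and of the logistic sequence alone, but not of the two together. If either may support a claim, the error is about 7–8% for Program 1 and about 6–8% for a null Program 2 when Program 1 works. These sizes depend on score distributions, a correlation between the tests and sham response rates that the article does not give; the range over the settings tried is narrow.

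Separately, and without any assumed figures, the COPM performance score subsection applied model by model conflicts with the Program 2 rule in Sample size {14}. Sizing on responders while naming mean change as primary does not by itself raise the error; it matters here because it leaves unclear which analysis decides.

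**What to change.** In the COPM performance score subsection, state that the week-8 ITT ANCOVA of change, Program 1 versus sham, is the sole gatekeeper at two-sided 5%, and that the same ANCOVA for Program 2 versus sham follows only if it succeeds. Label the COPM-P responder regressions supportive, with no gate of their own; if a responder claim is wanted, place it after those two steps in the same sequence. Record this before the group comparisons are examined.

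This restores 5% by construction and brings the subsection into line with Outcomes {12} and with the Program 2 rule in Sample size {14}. It takes one or two sentences and no further participants or data. The sponsor gives up a stand-alone responder claim when the ANCOVA fails. In the simulated settings with a 1.5-point Program 1 effect, the ANCOVA was significant in 92–96% of trials and the logistic regression in 76–82%. Under those assumptions, the main claim loses nothing by resting on the ANCOVA.
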